**4.1.3 Exclusion Criteria**

- Previous cervical surgery
- Any cervical pathology at 12 o’clock position on cervix
- Vaginal bleeding evident on examination
- Visible, symptomatic cervical or vaginal infections
- Known congenital uterine anomalies
- Known or suspected structural/chromosomal fetal abnormality
- Known HIV
- Cervical carcinoma

**4.1.4 Withdrawal Criteria**

We do not have formal stop criteria for the CASPAR study. However, we will establish a SMG which will meet at least monthly and will have the authority to recommend a halt to recruitment should there be concerns about patient safety.

In consenting to take part in the study, participants are consented to a speculum examination for cervical stiffness assessment and associated data collection and follow-up on pregnancy outcomes. If voluntary withdrawal occurs the participant should be given appropriate care until discharge.

The critical data in CASPAR study is derived from cervical stiffness measurement. Although participants can refuse examination at any time, refusal to have cervical stiffness measurements result in significant compromise to the study. Therefore, any participant who does not have cervical stiffness measurements would need to be withdrawn from the study. During the study procedure prior to cervical stiffness measurement, the cervix is inspected for any previously unknown cervical pathology at 12 o’clock position, new vaginal bleeding or visible cervical or vaginal infections. If any of these are present, the assessment cannot be undertaken based on manufacturer guidelines for use of the medical device. The patient would then be withdrawn from the study based on cervical criteria.

Foreseeable reasons where a participant may withdraw from the study generally apply to the additional need for a speculum examination and collection of cervical stiffness measurements and include:

- Participant withdraws consent,
- Newly diagnosed cervical criteria at time of study procedure
- Loss of capacity during the study, and
- Any other change in the participant’s condition that justifies the discontinuation in the clinician’s opinion.

A participant is free to withdraw from the study at any time. In addition, the CI may decide, for reasons of medical prudence, to withdraw a participant. In either event, the Sponsor will be notified and the date and reason(s) for the withdrawal will be documented in the participant source data. If a participant withdraws or is withdrawn, ideally, they should remain in the study for the collection outcome data. Generally, follow-up will continue unless the participant explicitly also withdraws consent for follow-up.

Participants who withdraw from the study for other reasons will be given routine standard care until delivery and will be asked to allow analysis of already anonymised data and collection of pregnancy outcome data. If the participant explicitly states their wish not to contribute further data to the study, collected data will be removed from the study database.

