**3.2 STUDY OUTCOME MEASURES**

**Feasibility Outcomes**

Our feasibility outcomes of interest relate to whether the study procedure is acceptable, participant recruitment is achieved, data collection is feasible, and cervical stiffness assessment fidelity is maintained with adequate reliability and safety(25).

Our feasibility outcomes will be defined as follows;

1. Recruitment rate
   1. Measured as proportion of participants recruited compared to total number approached for recruitment in the study period
   2. Reasons for non-participation collected
2. Participant acceptability of cervical stiffness assessment at IOL
   1. Qualitative questionnaire following assessment
   2. Number of participant withdrawals throughout the study duration
3. Adherence to protocol and data collection
   1. Measured as number of protocol deviations
   2. Missing data
4. Cervical stiffness fidelity
   1. Ability to obtain triplicate cervical stiffness measurements
   2. Triplicate measurement reliability

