**10.4.9 Withdrawals/ Losses to Follow Up and Missing Data**

The Study Co-Ordinator will produce reports on withdrawals, losses to follow-up and the quantity of missing CRF data across sites for review by the SMG. Identified problems will be discussed and remedial action taken as necessary.

As outlined in the data management plan, the Study Co-Ordinator will check that withdrawal CRFs are completed for all withdrawn participants (including the reasons for withdrawal). The Study Co-Ordinator will review withdrawal rates and reasons for withdrawal, paying particular attention to withdrawals close to dates of registration. If LWH experiences an excessive rate of withdrawals, additional training on the informed consent procedure will be provided.

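### Section 4.1.4 removes data already collected from the study database when a woman declines only to give further data, which can make acceptability look slightly better than it was

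*Protocol*

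**What the plan says.** Three statements in Protocol section 4.1.4 bear on a woman who withdraws.

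- On follow-up: "Generally, follow-up will continue unless the participant explicitly also withdraws consent for follow-up". Data already held are not mentioned.
- On women who withdraw for other reasons: they "will be asked to allow analysis of already anonymised data and collection of pregnancy outcome data". This names two permissions, one for existing data and one for future data.
- Directly after that: "If the participant explicitly states their wish not to contribute further data to the study, collected data will be removed from the study database".

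The same section says that the "date and reason(s) for the withdrawal will be documented in the participant source data". Section 3.2 lists "Number of participant withdrawals throughout the study duration" as a feasibility outcome under acceptability, next to a post-assessment questionnaire. It also lists the reliability of the triplicate readings. Section 10.4.9 requires a withdrawal CRF for every withdrawn participant and adds: "The Study Co-Ordinator will review withdrawal rates and reasons for withdrawal, paying particular attention to withdrawals close to dates of registration". Section 10.3.1 has all paper CRFs transcribed into the study database. Section 6.5.3 specifies a complete-case analysis without imputation or other adjustment.

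**The concern.** The trigger and the action in the removal sentence do not match. A woman who has had her three readings, filled in the questionnaire and then wants no more data taken has said nothing about what she has already given. The rule as written nevertheless takes it out of the database. Staff at the site also face two instructions for nearly the same event: stop follow-up, or stop follow-up and remove what is there.

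This matters because acceptability is an outcome of this feasibility study, and the loss is confined to withdrawers. Section 4.1.4 itself expects withdrawals to relate mainly to the extra speculum examination and the stiffness measurement. Women who leave after the assessment may therefore be less content with it than those who stay. If their answers leave the database, the remaining answers are more favourable than the experience of the whole cohort.

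**Working it through.** The protocol gives no withdrawal rate, acceptability target or sample size calculation, so there is no stated figure to reproduce. The check is of the text, followed by an illustration on assumed numbers.

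**Text, side by side**

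1. Existing and future data are two permissions in the sentence before the removal rule. A woman can grant the first and refuse the second. The rule makes refusal of the second enough to lose the first.
2. The follow-up sentence attaches one consequence to withdrawn follow-up consent: follow-up ends. The removal rule attaches a further one to what may be the same statement by the woman.
3. Data exposed: section 14.2 places the stiffness assessment, Bishop's score and questionnaire at one attendance, so a woman who withdraws afterwards may already have given all three. Section 10.3.1 has CRFs transcribed within 24 hours of the visit. I assume that questionnaire answers are entered in the same database; the protocol does not say so expressly.
4. Adverse events: non-serious events go on the CRF (section 5.6.1) and need no formal reporting (section 5.2), so they are exposed. SAEs go on a separate form to the study co-ordinator (sections 5.2 and 5.6.2).
5. Withdrawal record: date and reason are in source data (section 4.1.4), and section 7.6 adds an end of study form. The withdrawal CRF, however, is a CRF, and no section exempts it from removal from the database.

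**Illustration (all inputs assumed except N = 100)**

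Let A women of N = 100 find the assessment acceptable, and let k dissatisfied women be removed. This is the worst case, because every removed woman is dissatisfied.

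- All kept: A/N. After removal: A/(N − k). Shift: A·k / [N(N − k)].

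| A | k | All kept | After removal | Shift (points) |
|---|---|---|---|---|
| 90 | 1 | 90.0% | 90/99 = 90.9% | 0.9 |
| 90 | 2 | 90.0% | 90/98 = 91.8% | 1.8 |
| 90 | 5 | 90.0% | 90/95 = 94.7% | 4.7 |
| 80 | 1 | 80.0% | 80/99 = 80.8% | 0.8 |
| 80 | 2 | 80.0% | 80/98 = 81.6% | 1.6 |
| 80 | 5 | 80.0% | 80/95 = 84.2% | 4.2 |

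For 90/100 the Wilson 95% interval is 82.6% to 94.5%; for 90/95 it is 88.3% to 97.7%. With one or two women removed, the shift is well inside the sampling uncertainty. If removed women were as satisfied as the rest, no shift would be expected.

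Only if the withdrawal record were erased as well would the withdrawal count suffer: 5/100 (Clopper-Pearson 95% interval 1.6% to 11.3%) would appear as 0/95 (upper limit 3.8%). The protocol does not order that; it merely fails to rule it out for the database copy.

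**The case against.** The best defence is that the removal sentence is loosely worded and describes a woman who refuses both permissions just put to her. On that reading nothing is lost that she had agreed to give, and removal is a choice that protects participants. This is a possible intention, but the words name only further data, and staff will apply the words.

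The group at risk is also narrow. Women who refuse the speculum examination have no readings to lose, and later data come from routine records. The rule reaches only a woman who completes the assessment and then also refuses passive record review. Section 3.3 anticipates no loss to follow-up, and section 3.2 calls the questionnaire qualitative, so a percentage acceptable is not a stated planned estimate. All of this stands, and it limits the size of the problem.

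A reader might infer four stronger things that the documents do not support:

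- **Everything is destroyed.** Removal is from the study database. Source data, paper CRFs and SAE forms are not said to be destroyed.
- **Withdrawal reporting is contradicted.** Date and reason stay in source data, and section 10.4.9 has the study co-ordinator, who "will produce reports on withdrawals, losses to follow-up and the quantity of missing CRF data across sites for review by the SMG". The count in section 3.2 can be obtained from these. What remains is an open question about the database copy of the withdrawal CRF.
- **Serious safety data are lost.** SAEs travel by their own route, within 24 hours of awareness, with three-monthly line listings (section 5.6.3).
- **Reliability is biased in the device's favour.** Readings would be lost, but nothing in the protocol links withdrawal to poorer agreement between the three readings, so no direction can be claimed.

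**Conclusion.** The point holds in a limited form. The removal rule in section 4.1.4 does not fit the two-permission request before it or the follow-up rule earlier in the section. Read literally, it selectively removes questionnaire answers, stiffness readings and CRF-recorded non-serious adverse events of women who withdraw after the assessment, under an analysis that makes no correction.

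The effect on acceptability can only be favourable if the removed women are less satisfied than the rest. That is plausible but not shown. Its size is unknown and probably small: about 1 to 2 percentage points for one or two dissatisfied women of 100, and 4 to 5 points for five, on assumed worst-case inputs. The main outcome of concern is acceptability; the withdrawal count and SAE data have other sources.

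A smaller slip sits in the same paragraph. It describes the data as anonymised, whereas section 7.3 describes pseudonymised CRFs with a key. Truly anonymised data could not be traced to one woman and removed.

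This is not a matter to leave to a statistical analysis plan, because the rule acts on the database before any analysis begins.

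**What to change.** Amend section 4.1.4 to separate the two cases.

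- **Declines further data:** stop new collection from that date; retain and analyse data collected up to then.
- **Explicitly withdraws permission to use existing data:** remove those data from the study database.
- **In either case:** keep and count the withdrawal record (date, and reason if given) and any reported adverse events, and report how many women's data were removed.

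Align the follow-up sentence in the same section with this, change anonymised to pseudonymised in line with section 7.3, and match the wording in the information sheet and consent form, which are not available here.

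The cost is a short protocol amendment with matching participant documents. The small downside is that women must be told at consent that data collected before withdrawal are kept unless they ask for removal.

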**4.1.5 Patient Transfers**

This is not anticipated during the course of this study

**4.1.6 Stopping Criteria**

There are no formal stopping criteria for this study. The need to stop the study will be determined by the SMG and the decision will be based upon data integrity and participant safety.

**4.1.7 COVID precautions**

Liverpool Women’s NHS Foundation Trust is well prepared to deal with the impact of COVID-19 and as such has adopted a number of measures that are intended to keep visitors and staff safe. These include performing temperature checks at the entrance to the hospital, asking staff and visitors to use antibacterial hand gel and wear medical face masks that are provided at the door.

In addition, all study participants will be asked if they are experiencing any symptoms of potential COVID-19 infection, such as persistent cough, loss of taste or sense of smell or a fever/increased temperature. Staff at LWH are required to wear medical facemasks, disposable aprons and gloves whilst they care for study participants, regardless of the COVID-19 swab result.

**4.2 RECRUITMENT**

**4.2.1 Participant selection**

The majority of participants will be recruited directly from the induction of labour suite when they attend for their planned induction of labour. We will also endeavor to recruit patients when the induction of labour is booked during an attendance in antenatal clinic, during an inpatient admission, or attendance to the maternity assessment unit. At the time of identification, a member of the core clinical research team on site will be contacted and will attend to discuss their potential participation. Participants will be given written and verbal information on the CASPAR study, as well as an opportunity ask questions and take any additional time required to consider taking part in the study.

All patients that are identified as eligible and are then approached for the study will be included in the recruitment rate. Those that agree to participate will go on to enrolment and registration (see 4.2.3).

**4.2.2 Informed Consent**

On meeting a member of the research team, potential participants will be provided with an additional PIS to refer to, the opportunity to ask questions, discuss study objectives, risks and inconveniences of the study and the conditions under which the study is to be conducted. More time will be offered for consideration of participation if necessary and it will be made clear to the participant that the quality of medical care will not be adversely affected if they decline to participate in this study and they may withdraw from the study at any time.

Once a participant is happy to consent, they will be asked to sign the study-specific Informed Consent Form (ICF) in the presence of a member of the research team. Three copies of the consent form will be collected, the original given to the participant, one placed within the participants hospital notes and one held at the Centre for Women’s Health Research (CfWHR). The principal investigator (PI) will be required to review and sign all consent forms.

The PI will ensure that all members of the research team obtaining consent comply with applicable regulatory requirements, adhering to GCP and to the ethical principles that have their origin in the Declaration of Helsinki. Members of the research team will also have received study specific training relating to eligibility screening and the informed consent / registration process and CV’s will be reviewed of all team members to ensure adequate experience in gaining consent in a research capacity.

The PIS sent to potential participants has been reviewed by our Liverpool Babies PPI group who assisted on layout, language and formulation of lay explanations to make it easily understood. In addition, previous PIS and consent forms used in singleton preterm birth studies at the LWH were reviewed to see what format of information is acceptable for participating women.

**4.2.3 Enrolment and registration**

Once eligibility has been confirmed by the PI at site the participant will be registered onto the study using an electronic registration platform. Although it will be recommended that participants take a minimum of 24 hours to consider taking part in this study, the provision for allowing participant consent within a shorter period-of-time will be permitted- this is to reduce the number of examinations the patient undergoes, ensuring the cervical stiffness assessment will be done at the same time as the routine digital vaginal examination prior to commencement of the induction of labour. Documentation of reasons for non-inclusion will be detailed in the site screening logs and forwarded to the Research Manager at the CfWHR.

Once a participant consents to taking part in the study, they will be registered on a bespoke electronic data capture system that will generate a unique participant identification number (PIN).

**5. ADVERSE EVENTS**

**5.1 DEFINITIONS**

**5.1.1 Adverse Event (AE)**

An AE is defined as any untoward medical occurrence (i.e., any unfavourable or unintended sign including abnormal laboratory results, symptom or disease) in a research participant taking part in a clinical research study.

**5.1.2 Serious Adverse Event (SAE)**

An SAE is defined as any untoward and unexpected medical occurrence or effect that

• results in death,

• is life threatening – refers to an event in which the participant was at risk of death at the time of the event. It does not refer to an event which hypothetically might have caused death if it were more severe,

• requires hospitalisation or prolongation of existing inpatient hospitalisation,

• results in persistent or significant disability or incapacity

• Is a congenital anomaly or birth defect, and

• Is otherwise considered medically significant by the investigator

Medical judgement should be exercised in deciding whether an AE is serious in other situations. Important AEs that are not immediately life‐threatening or do not result in death or hospitalisation but may jeopardise the participant or may require intervention to prevent one of the other outcomes listed in the definition above, should also be considered serious.

**5.2 REPORTING PROCEDURES**

All AEs for this study will be recorded at each study visit on the study case report form (CRF). This study does not require the formal reporting of any non-serious AEs. This is a non-interventional study. We therefore do not anticipate a large number of SAEs.

Investigators must report all SAEs from enrolment to the end of the study. In addition, maternal death and maternal life-threatening complications, stillbirths and neonatal deaths are also pre-specified outcomes to be reported immediately as SAEs. All deaths reported as SAEs as part of this study will be reviewed regularly by the SMG and Sponsor. Urgent reporting of any SAEs in relation to the study medical device or study procedures are required. All SAEs must be reported within 24 hours of sites becoming aware of the event. Reporting should be completed by downloading the XXX study SAE form from the study file repository within REDCap, completing all fields on the form and then send it to the Study Co-Ordinator at the CfWHR. All SAE’s will be subject to regular review by the SMG.

**5.3 NOTES ON GRADING OF ADVERSE EVENTS**

The assignment of the severity/grading should be made by the investigator responsible for the care of the participant using the definitions below. Regardless of the classification of an AE as serious or not. Its severity must be assessed according to medical criteria alone using the following categories.

**Table 1. Grading of Adverse Events**

| **Grading** | **Criteria/Guidelines** |
| --- | --- |
| **Mild** | Does not interfere with routine activities (awareness of symptoms or signs, but easily tolerated [acceptable]). |
| **Moderate** | Interferes to some extent with routine activities (enough discomfort to interfere with usual activity [disturbing]) |
| **Severe** | Impossible to perform routine activities (incapacity to work or to do usual activities [unacceptable]) |
| **Life Threatening** | Results in risk of death, organ damage, or permanent disability (unacceptable) |
| **Death** | Results in death (unacceptable) |

A distinction is drawn between serious and severe AEs. Grading is a measure of intensity (see above) whereas seriousness is defined using the criteria in section 8.1 hence, a severe AE need not necessarily be a SAE.

**5.4 RELATIONSHIP TO STUDY PROCEDURES**

The assignment of the causality / relatedness should be made by the investigator responsible for the care of the participant using the definition in table 3 below. If any doubt about the causality / relatedness exists the local investigator should notify the CI. In the case of discrepant views of causality between the investigator and other, the Sponsor, HRA and REC will be informed of both points of view within the regulatory reporting timeframes.

**Table 2. Definition of Relatedness**

| **Relationship** | **Description** |
| --- | --- |
| **None** | There is no evidence of any causal relationship. N.B. An alternative cause for the AE should be given. |
| **Unlikely** | There is little evidence to suggest there is a causal relationship (e.g. the event did not occur within a reasonable time after administration of the study intervention). There is another reasonable explanation for the event (e.g. the participant’s clinical condition, other concomitant treatment). |
| **Possibly** | There is some evidence to suggest a causal relationship (e.g. because the event occurs within a reasonable time after the study intervention). However, the influence of other factors may have contributed to the event (e.g. the participant’s clinical condition, other concomitant treatments). |
| **Probably** | There is evidence to suggest a causal relationship and the influence of other factors is unlikely. |
| **Highly Probable** | There is clear evidence to suggest a causal relationship and other possible contributing factors can be ruled out |

